**Mass**

**Ladder**

134bp 138 bp

**Collection of samples**

# Tumor samples

Pre-treatment samples can be collected up to 2 weeks prior to starting treatment. The post-treatment sample should be collected 18-48 hours after the first treatment cycle. Although in some patients it will be possible to sample the same tumor pre-treatment and post-treatment, in most patients different tumors will be sampled. It is ideal to obtain multiple pre-treatment and post-treatment samples, an attempts will be made to carry this out.

The pre-treatment and post-treatment melanoma tumor samples will fixed in formaline and parffim embedded. Samples will be trimmed of obvious non-melanoma tissue. If there is a sufficient amount of normal skin associated with the sample, the normal skin may be stored separately and analyzed. Ideally, tumors biopsy will be approximately 1cm3. If larger samples are obtained, they will be split in duplicate. Blocks will be labeled with the patient’s name, protocol site (e.g NYU, Chicago university, Cornell ), date of collection, and an indication whether the sample was pretreatment or post-treatment.

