**11. STATISTICAL CONSIDERATIONS**

**11.1 Endpoints**

Primary endpoint:

- Response rate (RR)

Secondary endpoints:

- Time to progression (TTP)
- Toxicity
- Correlative Data
  1. **Study Design / Stratification Factors**

*Clinical Endpoints*

The primary endpoint of this trial is response rate defined as is either a complete or a partial response at the end of second cycle, using the RECIST criteria.

The response rate for standard of care DTIC is 5-10%. If the response is < 5%, the new treatment will not be considered for further study.

In each subgroup defined by BRAF status, a minimax two-stage Simon design will be used to test the null hypothesis that response rate at the end of second cycle (56 days) is p  0.05 versus the alternative that the response rate is p ≥ 0.20. If the drug is actually not effective, there is 3.3% probability of concluding that it is (the target was 5%). If the drug is actually effective there is a 14.2% probability of concluding that it is not (the target was 20%). After testing the drug on 13 patients per BRAF subgroup in the first stage, the trial will be terminated if 0 patients per subgroup respond. If the trial goes on to the second stage, a total of 37 patients per BRAF subgroup will be studied. If the total number responding is less than or equal to 4 patients per subgroup, the drug is rejected for that subgroup.

The overall response rate along with subgroup-specific response rates will be estimated at the end of the trial along with 95% confidence interval.

*Correlative Study Endpoints*

An important goal of this trial is to evaluate the biological markers pre and post treatment. Eligibility for the first stage of the trial (first 13 patients in each subgroup) requires that patients have biopsiable sites of disease. Tumor tissue will be collected and assessed for change in BRAF, P-MAPK, CDK4, and Cyclin D1 levels pre versus post treatment by analyzing the changes in the intensity of the specific bands on immunoblot. This is usually done visually (increase, no change, decrease) but can be quantified using a digital scanner. It is critically important to ensure that equal amounts of protein are loaded on to each lane. This can be confirmed by comparing the intensity of the p85 PI3k bands. The proportion of patients with decreases in levels of BRAF, CDK4, or phospho-MAPK will be estimated along with 95% confidence intervals.

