Cyclin D1 and phospho-MAPK expression will also be assessed by immunohistochemistry. The percentage of tumor cells staining for either marker will be quantified visually and expressed as a percentage of positively-staining tumor cells. In this study, we are measuring phospho-MAPK both by immunoblotting and by immunohistochemistry. These two techniques are complimentary in that immunoblotting measures the relative amount of phospho-MAPK in the tumor while immunohistochemistry gives information as to the percentage of cells expressing the protein.

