**Appendix D**

**Tumor Immunohistochemistry**

Immunohistochemistry of Cyclin D1: Staining for cyclin D1 will be carried out in [name] laboratory.  Formalin-fixed paraffin-embedded sections will be cut at 4-5 microns placed on Superfrost/Plus slides (Fisher) and baked at 60oC for at least 60 minutes. Slides will be deparaffinized and hydrated in distilled water. Then the slides will be washed, quenched of endogenous peroxidase, and washed again in saline followed by phosphate-buffered saline (PBS). Slides will be then placed in a solution containing 0.005% bovine serum albumin (BSA) followed by normal serum at 1:20 dilution in 2% BSA/PBS. A 150 mLvolume of a 1:100 dilution of the primary antibody is placed on the tissue and incubated overnight (15-18 hours) at 40oC in a humidity chamber. After several washes in PBS, a secondary antibody is applied for 60 minutes at a dilution of 1:500 in 1% BSA/PBS.  Peroxidase-conjugated streptavidin (1:500 in 1% BSA/PBS) is then applied for 45-60 minutes, followed by several washes in PBS. Diaminobenzidine at 0.06% is used as the chromogen, and Harris-modified hematoxylin (Fisher) is used for counterstain. In addition, we will measure phosphorylated-MAPK and phosph-ERK by immunohistochemistry using an antibody to the activated, phosphorylated MAPK (Cell Signaling Technology, Beverly, MA). For positive Cyclin D1 controls, we typically use a positive bladder cancer or prostate cancer specimen, as we have described previously(27,29).  Prostate cancer is typically positive for phospho-ERK staining and we plan to identify tumor samples that will serve as positive controls.  Negative controls are specimens stained with isotype-specific control primary antibody. We will obtain a quantitative assessment of the degree of antibody staining employing Kodak ID image analysis software.

Appropriate antigen retrieval will be performed for each of the markers in 0.1mM citrate buffer at pH 6. The immunostaining will be performed using the avidin biotin peroxidase complex method (ABC) using a semi-automated immunostainer (NexES, Ventana Medical Systems, Tucson, AZ). Secondary detection uses conventional, well-established avidin-biotin horseradish peroxidase complex with 3,3 diaminobenzidine (DAB) as the chromogen. The immunohistochemistry images from five defined regions of the stained tumor slides are to be captured at 60X magnification using an Olympus BX40 microscope and DP11 digital image system as JPEG files.

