The intensity of immunohistochemical staining for each of the respective markers is quantified via a three step procedure that involves the following: 1) The analysis of the JPEG photomicrograph image using Adobe Photoshop (San Jose, Ca) to process the immunohistochemictry densities through the use of the magic wand tool to extract the stained tissue color essentially as detailed by Matlowsky et al (2004) followed saving the processed image in a TIFF file format. 2) The Photoshop processed images were analyzed using Kodak ID image analysis software (Kodak Imaging systems, Rochester, NY) employing the “density slice method” for quantification of the pixel density in the regions of interest (ROI) correlating to the immunohistochemistry positive staining for each marker. 3) The “summation of intensity values” from the Kodak ID density table were exported via a text format to Microsoft Excel (Microsoft Corp, Redman Washington) where the summation of the identified ROIs was carried out.

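### Tissue blocks must show the patient's name and time point, the markers are read largely by eye, no masked reading is specified, and the protocol gives two different immunohistochemistry readouts

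*Protocol*

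**What the plan says.** **Labelling.** Appendix C (Collection of samples, Tumor samples) states: "Blocks will be labeled with the patient’s name, protocol site", followed by the "date of collection, and an indication whether the sample was pretreatment or post-treatment". Section 10.1 gives every patient an identification number at registration, but the block label does not use it.

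**Immunoblot reading.** Section 11 (Correlative Study Endpoints) says of the change in band intensity: "This is usually done visually (increase, no change, decrease) but can be quantified using a digital scanner". The summary is then: "The proportion of patients with decreases in levels of BRAF, CDK4, or phospho-MAPK will be estimated along with 95% confidence intervals".

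**Immunohistochemistry reading.** The same section says of cyclin D1 and phospho-MAPK: "The percentage of tumor cells staining for either marker will be quantified visually". Section 7.2 instead describes quantitative immunohistochemistry, and Appendix D says: "We will obtain a quantitative assessment of the degree of antibody staining employing Kodak ID image analysis software". The first step of that image analysis is done by an operator, "through the use of the magic wand tool to extract the stained tissue color".

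**Masking.** The protocol does not mention masked marker readers, recoded slides or a second reader. Independent review appears only for tumour response (Section 9.6).

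**The concern.** Objective 1.4 asks whether the drug depletes the pathway proteins in the tumour. The evidence is a before-and-after comparison within each patient, with no control arm, and the expected direction is stated in advance. The result is a proportion of patients with a decrease. In that setting, a reader who knows which specimen is post-treatment and judges borderline cases by eye can push the result only one way, and the confidence interval will not show it.

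The required label gives away the time point, and the statistical section describes the more subjective reading. Appendix C adds room for judgement, because in most patients the two biopsies will come from different tumours and multiple samples are sought.

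The disagreement on readout is a separate fault. A percentage of positive cells estimated by eye and a summed pixel intensity are different quantities. Two people following different parts of this protocol could report different immunohistochemistry results from the same slides. Patients undergo paired punch or excisional biopsies for this objective.

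**Working it through.** The protocol states no precision or error figure for the marker endpoints, so there is nothing to reproduce. The check has two parts: a comparison of the texts, and arithmetic on how much reading error matters at this sample size.

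**1. Which tissue and which reading each text covers**

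| Assay | Tissue | Reading in Section 11 | Reading elsewhere |
|---|---|---|---|
| Immunoblot | Snap-frozen portion (Section 4.1.2) | Usually visual, three categories; digital scanner optional | None given |
| Immunohistochemistry | Formalin-fixed portion, in paraffin blocks (Section 4.1.2, Appendix C) | Visual percentage of positive cells | Image analysis (Section 7.2, Appendix D) |

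The block label bears directly on immunohistochemistry only. The decrease call is described for the immunoblot, whose frozen tissue has no labelling rule in the protocol. Section 7.2 blurs the split: it says quantitative immunohistochemistry removes the need to handle frozen tissue, then refers to immunoblotting that still needs tissue. Phospho-MAPK is measured by both methods. Neither assay has a stated masked reading.

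**2. Effect of single calls**

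Input: 13 biopsied patients per subgroup (Section 4.1.2).

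- One call: 1/13 = 7.7 points.
- Two calls: 2/13 = 15 points. Three calls: 3/13 = 23 points. That two or three pairs would be affected is an assumption; the documents give no reading-error rate.
- Approximate 95% half-width at 50%: 1.96 × √(0.25/13) = 0.27, or 27 points.
- Ratio: 0.154/0.272 = 57%; 0.231/0.272 = 85%. The shift is thus 57 to 85% of the half-width. Against the full width of about 54 points it is 28 to 42%.
- Exact (Clopper-Pearson) intervals: 5/13 = 38% (14 to 68%); 7/13 = 54% (25 to 81%). Two changed calls take the estimate from one to the other.

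**3. Effect of a one-sided misreading rate**

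Let q be the true share of pairs with a decrease and m the share of the remaining pairs that are read as a decrease. Both are assumed.

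Read share = q + (1 − q) × m

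| True share q | m = 10% | m = 20% | m = 30% |
|---|---|---|---|
| 33% | 40% | 47% | 53% |
| 50% | 55% | 60% | 65% |

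The shift (1 − q) × m does not depend on the number of patients. Pooling both subgroups (26 pairs) narrows the interval, for example 13/26 = 50% (30 to 70%), but leaves the bias unchanged.

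**The case against.** The strongest objections are these.

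- **The protocol does not say that readers are unmasked.** It labels blocks. Reading is done on sections mounted on slides, and the text is silent on slide labels and on what the reader sees. A reader might infer that the endpoint is read unblinded, but the documents do not support that. They support only that the required label reveals the time point and that no masked reading is specified. This objection stands and limits the claim.
- **The block label does not reach the decrease call.** That call belongs to immunoblots of frozen tissue. This also stands. The remedy therefore has to cover frozen aliquots and immunoblot reading; relabelling blocks alone would miss the stated proportion. The lack of any masking applies to both assays.
- **Image analysis already solves the problem.** It does not. One might infer that a coded, software-based reading is already available, but no coding is described, and the colour-selection step depends on an operator who is not stated to be masked.
- **The endpoint is secondary and exploratory.** True: Section 11 lists correlative data as secondary and Section 11.4 analyses them descriptively. They do not enter the response rate or the two-stage rule. This limits the weight of the point but does not remove it, since Section 11 also calls marker evaluation an important goal.
- **Masking is often left to a laboratory manual or the SAP.** Fair for masking as such. But here the protocol itself orders a revealing label and contradicts itself on the readout, and both need correcting in the protocol.

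**Conclusion.** The point holds in a limited form. The protocol orders a label that reveals name, collection date and time point, plans visual reading of both assays in its statistical section, specifies no masking, and disagrees with itself on how immunohistochemistry is read. In an uncontrolled comparison with a predicted direction, this leaves objective 1.4 open to reader-expectation bias.

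One call in 13 is worth 7.7 points. Two or three calls are worth 15 to 23 points, 57 to 85% of the 27-point half-width. It would be wrong to describe this as nearly the whole confidence interval. The number of affected pairs and the misreading rates are assumptions. Nothing in the documents shows that biased reading has occurred or how large it would be.

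This is a cheap improvement to a secondary, exploratory endpoint. The primary response rate and the two-stage decision rule are unaffected. Masking removes reader expectation only; it does not remove differences between the separate tumours sampled before and after treatment.

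**What to change.** 1. **Appendix C.** Label blocks, slides and frozen aliquots with the registration number plus a random specimen code. Take the name, collection date and pre/post status off the label. The key is held away from the reader, for example by the Coordinating Center, until scoring is locked.
2. **Section 11.** State that immunoblot and immunohistochemistry reading is masked to time point and to clinical response, and that this includes the operator's colour-selection step in the image analysis.
3. **Sections 7.2 and 11 and Appendix D.** Reconcile the readouts. Make the Appendix D image-analysis value the immunohistochemistry readout, and the digital scanner value that Section 11 already names the immunoblot readout. Define a decrease for each before scoring starts, and keep visual scores as descriptive. The documents give no assay variability from which to set the threshold, so the laboratory would have to supply it.

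**Cost.** A code list to maintain, a short specimen-handling instruction for the sites that send tissue to the central laboratory, and a few sentences of text. No new patients, biopsies or assays are needed, and the registration number already exists. It also takes patient names off specimens in a multicentre study.

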**PBMC**

One tube of blood will be collected using Vacutainer CPT tubes (Becton Dickinson, Franklin Lakes, NJ) at the time of tumor collection, and just prior to treatment #2. In patients not undergoing tumor biopsy, PBMC will be collected just prior to treatment #1, 18-48 hours later, and just prior to treatment #2. The cells are processed as detailed in the Appendix describing the CPT processing steps.

**Appendix D**

**Tumor Immunohistochemistry**

Immunohistochemistry of Cyclin D1: Staining for cyclin D1 will be carried out in [name] laboratory.  Formalin-fixed paraffin-embedded sections will be cut at 4-5 microns placed on Superfrost/Plus slides (Fisher) and baked at 60oC for at least 60 minutes. Slides will be deparaffinized and hydrated in distilled water. Then the slides will be washed, quenched of endogenous peroxidase, and washed again in saline followed by phosphate-buffered saline (PBS). Slides will be then placed in a solution containing 0.005% bovine serum albumin (BSA) followed by normal serum at 1:20 dilution in 2% BSA/PBS. A 150 mLvolume of a 1:100 dilution of the primary antibody is placed on the tissue and incubated overnight (15-18 hours) at 40oC in a humidity chamber. After several washes in PBS, a secondary antibody is applied for 60 minutes at a dilution of 1:500 in 1% BSA/PBS.  Peroxidase-conjugated streptavidin (1:500 in 1% BSA/PBS) is then applied for 45-60 minutes, followed by several washes in PBS. Diaminobenzidine at 0.06% is used as the chromogen, and Harris-modified hematoxylin (Fisher) is used for counterstain. In addition, we will measure phosphorylated-MAPK and phosph-ERK by immunohistochemistry using an antibody to the activated, phosphorylated MAPK (Cell Signaling Technology, Beverly, MA). For positive Cyclin D1 controls, we typically use a positive bladder cancer or prostate cancer specimen, as we have described previously(27,29).  Prostate cancer is typically positive for phospho-ERK staining and we plan to identify tumor samples that will serve as positive controls.  Negative controls are specimens stained with isotype-specific control primary antibody. We will obtain a quantitative assessment of the degree of antibody staining employing Kodak ID image analysis software.

Appropriate antigen retrieval will be performed for each of the markers in 0.1mM citrate buffer at pH 6. The immunostaining will be performed using the avidin biotin peroxidase complex method (ABC) using a semi-automated immunostainer (NexES, Ventana Medical Systems, Tucson, AZ). Secondary detection uses conventional, well-established avidin-biotin horseradish peroxidase complex with 3,3 diaminobenzidine (DAB) as the chromogen. The immunohistochemistry images from five defined regions of the stained tumor slides are to be captured at 60X magnification using an Olympus BX40 microscope and DP11 digital image system as JPEG files.

The intensity of immunohistochemical staining for each of the respective markers is quantified via a three step procedure that involves the following: 1) The analysis of the JPEG photomicrograph image using Adobe Photoshop (San Jose, Ca) to process the immunohistochemictry densities through the use of the magic wand tool to extract the stained tissue color essentially as detailed by Matlowsky et al (2004) followed saving the processed image in a TIFF file format. 2) The Photoshop processed images were analyzed using Kodak ID image analysis software (Kodak Imaging systems, Rochester, NY) employing the “density slice method” for quantification of the pixel density in the regions of interest (ROI) correlating to the immunohistochemistry positive staining for each marker. 3) The “summation of intensity values” from the Kodak ID density table were exported via a text format to Microsoft Excel (Microsoft Corp, Redman Washington) where the summation of the identified ROIs was carried out.

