**7.0 CORRELATIVE/SPECIAL STUDIES**

**7.1** *BRAF* exon 15 and *NRAS* exon 3 will be sequenced from paraffin-embedded melanoma tumor tissues by the [name]/ [name] lab at NYU. In our published study, 92% of mutations in metastatic melanoma tissues were in BRAF exon 15. BRAF exon 11 will not be examined before treatment because our study indicated that only (2/77) 2.6% of metastatic melanoma tissues harbor this mutation. (Cancer Res. 2003 Jul 15;63(14):3955-7.) NRAS will be assessed despite its relatively rare occurrence (exon 3 mutations were found in only 4% of tumors in our study) because it functions upstream of BRAF. Activating mutations in NRAS, therefore, may lead to an increase in the level of BRAF activity and may explain why a patient with a wild-type BRAF tumor would response to treatment with BAY 43-9006.

We expect tumors from 6 or 7 patients to harbor a *BRAF* mutation and tumors from 1 or 2 patients to harbor an *NRAS* mutation. We anticipate that 2-3 patients will have no detectable mutation in either of these genes.

Representative tumor tissue sections will be sent to the [name]/[name] laboratory at NYU via hand delivery or overnight mail to ensure timely delivery. Genomic DNA will be extracted from paraffin tissue blocks using a Qiagen Tissue Kit (Qiagen, Valencia, CA). Exon 3 of N-RAS and exon 15 of BRAF will be amplified by PCR and sequenced using the methods described in our published paper. Turn-around time is expected to be within 10 days of receipt of tumor samples. (**Appendix C**)

**7.2** Tumor levels of CDK4, phospho-MAPK, and cyclin D1 will be assessed by our newly optimized quantitative immunohistochemistry. Expression of p85 PI3 kinase (expected to be unaffected by treatment) will be assessed as internal controls. (**Appendix D**).

These studies will be done using the formalin-fixed portion of the biopsies. By utilizing quantitative immunohistochemistry to determine relative alterations in protein expression levels, we eliminate the need for handling and delivery of frozen tissue. In addition, we will measure phosphorylated MAPK by immunohistochemistry using an antibody to the activated,phosphorylated MAPK (Cell Signaling Technology, Beverly,MA). These studies will be done using the formalin- fixed portion of the biopsies. As a result, these analyses will not exhaust tissues required for the immunoblotting studies described above.(**Appendix D**)

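### The immunohistochemistry score in Appendix D is an undivided sum of staining intensity, so its pre/post change mixes tumour content per field with protein level

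*Protocol*

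**What the plan says.** Appendix D (Tumor Immunohistochemistry) fixes the image sampling: "The immunohistochemistry images from five defined regions of the stained tumor slides are to be captured at 60X magnification". The second step of the scoring is "quantification of the pixel density in the regions of interest (ROI) correlating to the immunohistochemistry positive staining for each marker", so only stained areas enter. The third step exports the intensity totals to a spreadsheet, "where the summation of the identified ROIs was carried out". Nothing is divided by tumour area, cell count or a control stain, and Appendix D does not mention p85.

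Section 7.2 gives the purpose: "By utilizing quantitative immunohistochemistry to determine relative alterations in protein expression levels". It applies the method to CDK4, phospho-MAPK and cyclin D1. It also plans a control, "Expression of p85 PI3 kinase (expected to be unaffected by treatment) will be assessed as internal controls", and refers to Appendix D for the method, but gives no rule for using the control.

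Appendix C (Tumor samples) says of the pre- and post-treatment biopsies that "in most patients different tumors will be sampled".

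Section 11 (Correlative Study Endpoints) uses p85 only for the immunoblots, where equal protein loading is checked: "This can be confirmed by comparing the intensity of the p85 PI3k bands". For cyclin D1 and phospho-MAPK it describes a different immunohistochemistry readout, a visual count "expressed as a percentage of positively-staining tumor cells".

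**The concern.** Objective 1.4 asks whether treatment depletes these proteins inside the tumour. A sum over stained area equals stained area times intensity. Five fields holding less tumour give a lower sum even if every tumour cell stains exactly as before. Because most pairs come from two different lesions, tumour content will vary between the two biopsies for reasons unrelated to the drug.

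The same slides could also give two answers. If tumour fills 80% of the fields before and 50% after, with unchanged staining per cell, the Appendix D score falls by 37.5% while the percentage of positive tumour cells in section 11 does not move. CDK4 has no such percentage readout. At stake is the precision of the pathway comparison in a small set of paired biopsies, and the clarity of what an immunohistochemistry change means.

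**Working it through.** The protocol states no figure for this score, so there is none to reproduce. The check is of the structure of the score, followed by its size under stated assumptions.

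**Structure.** Let f be the fraction of the field filled by tumour, q the share of tumour that stains, and m the mean staining intensity. In units of one field area, the Appendix D score is

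S = 5 × f × q × m.

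With no drug effect, q and m are the same before and after, so S(post)/S(pre) = f(post)/f(pre). Dividing S by tumour-cell area (5 × f) leaves q × m, in which f no longer appears. Dividing by the p85 sum also removes f, provided p85 staining is proportional to tumour content.

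| f before | f after | Change in raw sum | Change per tumour area | Change per p85 sum |
|---|---|---|---|---|
| 0.8 | 0.6 | 0.6/0.8 − 1 = −25% | 0% | 0% |
| 0.8 | 0.5 | 0.5/0.8 − 1 = −37.5% | 0% | 0% |
| 0.8 | 0.4 | 0.4/0.8 − 1 = −50% | 0% | 0% |
| 0.4 | 0.8 | 0.8/0.4 − 1 = +100% | 0% | 0% |

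**Size under no drug effect.** These inputs are assumptions and do not come from the protocol:
- f is uniform over the stated range and independent before and after;
- staining noise e on the log pre/post ratio is normal with SD 0.15;
- p85 carries independent noise of the same size;
- tumour area is measured with little error;
- an apparent fall means a ratio below 0.7, and an equivalent rise means a ratio above 1/0.7 = 1.43.

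Raw ratio = [f(post)/f(pre)] × exp(e), by simulation of null pairs:

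| Range of f | Fall of 30% or more | Equivalent rise | Expected false falls in 13 pairs |
|---|---|---|---|
| 40-90% | 16.9% | 16.9% | 13 × 0.169 = 2.2 |
| 50-90% | 10.7% | about 10.8% | 13 × 0.107 = 1.4 |
| 60-90% | 5.5% | 5.5% | 13 × 0.055 = 0.7 |
| 70-90% | about 2.4% | about 2.4% | 13 × 0.024 = 0.3 |

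The two alternatives do not depend on the range of f and have closed forms, with ln 0.7 = −0.357:
- per tumour-cell area: Φ(−0.357/0.15) = Φ(−2.38) = about 0.9%, or 13 × 0.009 = 0.1 false falls in 13 pairs;
- per p85 sum: noise SD = √2 × 0.15 = 0.212, so Φ(−0.357/0.212) = Φ(−1.68) = about 4.6%, or 13 × 0.046 = 0.6.

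Falls and rises are equally frequent, so with independent sampling the fault is noise. Dividing by p85 helps clearly when tumour content varies widely (16.9% down to 4.6%) and hardly at 60-90% (5.5% to 4.6%). At 70-90% it does harm (2.4% up to 4.6%). Dividing by area does better than the raw sum at every range tried.

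**The case against.** The strongest reply is that the control exists. Section 7.2 plans p85 as internal control for this very work, and the formula for applying it could sit in a laboratory manual or analysis plan that is not shown. A reader might infer from Appendix D that the trial decided against normalising, or that p85 stains are already in hand. The documents support neither: p85 is planned, and Appendix D is simply silent on it. What remains is that Appendix D does write out the calculation through to its last step, and that step has no denominator.

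Second, no section makes the raw sum a formal endpoint. Section 11 counts patients with decreases on immunoblot, uses percent positive cells for immunohistochemistry, and treats the correlative endpoints as exploratory and descriptive. This stands and limits the reach of the point. It does not remove it, because section 7.2 says the quantitative score is what will show relative changes in expression, and it is the only immunohistochemistry readout described for CDK4.

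Third, a reader might infer that the raw sum favours the hypothesis, since less tumour reads as less protein. The documents do not support that as a general statement. They give no evidence that tumour content in the sampled fields falls after one cycle, and with independent sampling the error is symmetric and hides inhibition as often as it mimics it.

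Fourth, Appendix C trims obvious non-melanoma tissue, and Appendix D takes defined regions of the tumour slide. Both narrow the spread of tumour content. Neither fixes it within a field, so the lower end of the range above may be nearer the truth, but the confounding stays.

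**Conclusion.** The point holds as a fault in how Appendix D derives the score. As written, the score confounds protein level with tumour content, in a design where most pairs come from different lesions. The consequence is avoidable noise in both directions. It would become bias towards apparent inhibition only if tumour content fell systematically after treatment, which the protocol does not establish.

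The size cannot be fixed from the documents. Under the assumptions above, false falls of 30% or more run from about 17% of patients (tumour fraction 40-90%) to about 2% (70-90%) with the raw sum, against about 0.9% per tumour-cell area. The tumour fractions, the noise SD and the 30% cut-off are all assumed.

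The effect is confined to the exploratory immunohistochemistry part of objective 1.4. It does not touch the primary response rate, the two-stage design or the immunoblot readout. Separately, section 7.2, section 11 and Appendix D do not agree on what the immunohistochemistry measure is or how p85 enters it.

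**What to change.** In step 3 of the Appendix D scoring, divide each marker's summed intensity by the measured tumour-cell area in the same five regions. The denominator must be all tumour-cell area, stained and unstained; dividing by stained area alone would remove a real fall in the share of cells that stain. Analyse the pre/post change as the log ratio of these normalised scores.

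Report the ratio of the marker sum to the p85 sum as a sensitivity check. It should not be the main score, because it assumes p85 scales with tumour content and adds its own noise.

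Reconcile the text: let section 7.2 and Appendix D say the same about how p85 is used, and let section 11 state how the area-normalised score and the percentage of positive tumour cells relate, including which applies to CDK4.

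The cost is a small amount of extra image analysis to outline tumour on images that are captured anyway. No further biopsy is needed, and the p85 check uses a control already planned.
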